### Sample size

The sample size calculation is based on the improvement of MMSE scores, which is used as the primary effect indicators to estimate. According to the similar published articles [29], the mean difference in MMSE scores before and after treatment is three points, with a standard deviation of 1.5. According to our pilot study, a therapeutic regimen of TCM rehabilitation (CT + acupuncture) can probably improve the MMSE by 3.52 points on average compared to the control group. Improvement will be measured according to the same size of the estimation formula:1$$ \mathrm{n}=2\left[{\left({u}_{\alpha }+{u}_{\beta}\right)}^2{\sigma}^2\right]/{\delta}^2 $$

With a type I error of 5 % (α = 0.05) and 90 % power (β = 0.10), it is estimated that a sample size of 173 participants per group will be required. Considering a 20 % dropout rate during the study, a minimum of 416 total participants is needed to reach the target 208 participants per group.

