### Acupuncture therapy

The intervention group will be treated on two acupuncture points (Baihui (DU20) and Shenting (DU24)). The acupoint-location method is based on bone proportional cun. Bone proportional cun is mainly marked as the primary landmarks by using joints on the surface of the body; the length between the two joints will be discounted for a certain amount of discretion in order to determine the location of the acupoints. Baihui (DU20) is located on the head, 5 B-cun superior to the anterior hairline, on the anterior median line; or when the ears are folded, Baihui (DU20) is located at the midpoint of the connecting line between the auricular apices. Shenting (DU24) is located on the head, 0.5 B-cun superior to the anterior hairline, on the anterior median line.

Acupuncture will be performed by acupuncturists who are TCM licensed, and have at least three years of experience. The acupuncture procedure starts with the patient in the sedentary or supine position. After acupoint area sterilization, the acupuncturist’s left hand should fix the skin of the stimulus area, and the right hand should hold the disposable sterile acupuncture needle (Huatuo brand, model 0.30 mm × 25 mm, Suzhou Medical Appliance Factory, China). Then, the needle is inserted into the acupoints subgaleally from the front to the rear along the scalp, at an angle of 10 to 20 °, to a depth of approximately 25 to 35 mm. Following insertion, stimulation of the acupuncture point is applied until the *de qi* sensation is achieved, which means that patients experience a certain feeling with a mixture of sourness, numbness, distension, and pain from the acupuncture. The acupuncturist will use the manipulation technique with rapid twirling performed for two to three minutes every 10 minutes, at a frequency of 180 to 300 times/min. Meanwhile, CT will be performed constantly for 30 minutes throughout the acupuncture therapy. Following the treatment session, the needles will be withdrawn, and a dry sterilized cotton ball will be slightly pressed the holes of needles to avoid bleeding. The treatment will be given once a day for five times a week, lasting for 12 continuous weeks.

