### Statistical methods

All data will be analyzed using SAS version 8.2 (SAS institute Inc., Cary, NC, USA) by an independent blinded statistician. A statistical significance level of 0.05 will be used. For statistical description, continuous variables will be presented for each group using the mean ± standard deviation for normal distribution, and median and interquartile range for non-normal distribution. Categorical variables will be presented by using proportions with their standard error. In order to compare the primary and secondary outcomes between groups, measured at baseline, post-intervention and post-follow-up, the t-test or Mann–Whitney U test will be used for continuous variables and the Pearson chi-squared or Fisher’s exact test will be used for categorical variables. Non-parametric tests, Pearson chi-squared test, or Fisher’s exact test will be used for expressing changes in effect sizes of primary and secondary outcomes between groups before and after treatment, and during the follow-up period (at 12 weeks and 24 weeks).

To adjust the confounding influence if necessary, a general linear model or linear regression will be applied for dependent continuous variables, and a logistic regression model for dependent categorical variables. The analysis of the primary outcome will be expressed by using full analysis set with the principle of intention-to treat and the per-protocol set. The analysis of the secondary outcomes will be performed using the per-protocol set. The analysis of AE will be undertaken by using a chi-square test or Fisher’s exact test. Lastly, the economic evaluation will be assessed using cost-effectiveness analysis. Missing data will be imputed by the last observation carried forward rules.

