## Discussion

Post-stroke cognitive impairment is highly prevalent all over the world [16]. It significantly impairs patients’ participation in rehabilitation, engagement in daily activities, and their quality of life [55]. Meanwhile, the high economic burden that stroke rehabilitation imposes on family and society is growing [56]. Moreover current therapies, mainly CT and pharmacological treatment, lack sufficient evidence to support their effectiveness due to the complexity of cognitive impairment management [6]. The recent use of combined therapy has increasingly attracted attention, offering a new prospect in PSCI treatment [17].

Acupuncture is considered to be effective in improving cognition and has the advantages of being simple, convenient, efficient, and inexpensive, without severe adverse effects [20, 57]. A systematic review [58] has proposed that acupuncture improves cognitive function impairment in patients with PSCI, but the lack of high quality research has prevented the development of evidence-based recommendations for clinical practice. This review also recommends that future clinical trials should focus on the effect of acupuncture treatments combined with a second treatment, aiming to find the most cost-effective therapy combination that promotes the greatest improvement in stroke rehabilitation.

Previous studies have been limited by random methodology and small sample sizes [26, 27]. Thus, a prospective, multicenter, large sample, single-blinded, randomized controlled trial designed under strict systematic operational and high quality practices is needed to evaluate whether a therapeutic regimen of TCM rehabilitation leads to a more effective improvement in PSCI.

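### The named adverse event inference, a chi-squared or Fisher test, says little about uncommon harms or needle-only events; add risk differences and exact incidence intervals

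*Protocol article*

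**What the plan says.** The Statistical methods section of the protocol article gives adverse events one sentence: "The analysis of AE will be undertaken by using a chi-square test", with Fisher's test as the alternative. No risk difference, risk ratio or confidence interval is named for them. Two general rules in the same section also apply: "A statistical significance level of 0.05 will be used", and, for description, "Categorical variables will be presented by using proportions with their standard error".

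Other sections deal with safety conduct. Safety assessments has events documented in detail over treatment and follow-up, with serious events reported at once to the primary investigator and an ethics committee. Data collection and management sets up an independent monitoring board that acts on clinical judgment.

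The Sample size section rests on MMSE only. It states no adverse event rate, safety margin or power for a safety comparison.

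**The concern.** Only the intervention arm is needled: five sessions a week for 12 weeks, or 5 × 12 = 60 sessions per participant. The Acupuncture therapy section foresees one local event, since a cotton ball is "slightly pressed the holes of needles to avoid bleeding" after withdrawal. Needle-site events of this kind have a control rate of zero by design. Testing that zero against the intervention arm shows at most that needling causes needle-site events. A reader needs to know how often they occur and how high the true rate could be.

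For events that can occur in either arm, a test chosen without regard to event frequency will often be non-significant when the event is uncommon, whether or not there is an excess. The p-value does not say how large an excess remains compatible with the data. A proportion with its standard error helps when events are common, but it breaks down at or near zero events, where serious harms are most likely to lie.

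At stake is whether the safety results can bound the added risk of needling, or only state that no difference was shown.

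**Working it through.** **Inputs from the protocol article.** α = 0.05 (Statistical methods; sidedness is not stated, and two-sided is used here). From Sample size: power 90%, SD 1.5 MMSE points, 173 per group, 20% dropout, 208 per group. Allocation is 1:1 (Study design). Every adverse event rate below is an assumption.

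**1. The plan's own figure.** The article's formula is n = 2(u_α + u_β)²σ²/δ². The stated n is approached only with δ = 3.52 − 3 = 0.52:

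- two-sided: 2 × (1.960 + 1.282)² × 1.5² / 0.52² = 174.9, so 175, within two of the stated 173;
- one-sided: 143.

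This supports the two-sided reading. The step to 208 is 173 × 1.2 = 207.6. So 208 per arm comes from an efficacy calculation, and no safety quantity entered it. (The article words 3.52 as the difference from control, which does not match δ = 0.52; that is a separate matter.)

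**2. Power of the named test.** Exact enumeration of the two-sided Fisher test at 0.05:

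| Control v intervention | 208 per arm | 173 per arm |
|---|---|---|
| 0% v 1% | 2% | 1% |
| 0% v 2% | 24% | 14% |
| 0% v 3% | 60% | 42% |
| 0% v 5% | 95% | 87% |
| 1% v 2% | 5% | 3% |
| 1% v 3% | 18% | 13% |
| 2% v 4% | 14% | 11% |
| 5% v 10% | 42% | 35% |
| 5% v 15% | 92% | 85% |
| 10% v 20% | 79% | 70% |
| 10% v 25% | 98% | 95% |

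Power is poor for uncommon events and for doublings from 1%, 2% or 5%. It is good for several larger or commoner differences.

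**3. Events needed against none.** Fisher p at 208 per arm: 4 v 0, p = 0.123; 5 v 0, p = 0.061; 6 v 0, p = 0.030. Six events (6/208 = 2.9%) are needed to reach significance.

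**4. What the standard error shows.** SE = √(p(1 − p)/n).

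- 0 of 208: SE = 0, reported as 0% ± 0. The exact upper limit is 1 − 0.05^(1/208) = 1.4% (one-sided 95%) or 1 − 0.025^(1/208) = 1.8% (two-sided).
- 1 of 208: p = 0.48%, SE = 0.48%. Then p ± 1.96 SE runs from −0.5% to 1.4%, while the exact two-sided upper limit is 2.6%.

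**5. What an interval adds.** For 8 v 4 events of 208, Fisher p = 0.38. The risk difference is (8 − 4)/208 = 1.9 points, with Newcombe 95% interval −1.5 to +5.7 points. The p-value reports no significant difference; the interval shows that an excess of nearly 6 points is not excluded.

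**The case against.** Four points can be made for the plan.

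- **Testing is not all the article offers.** The descriptive rule, read generally, gives event proportions by arm. Event documentation, serious event reporting and the monitoring board do not depend on a p-value. This stands: the tests are the only *inference* named, not the whole of safety handling. It does not repair the zero standard error in step 4, and conduct safeguards do not estimate the excess risk.
- **The trial can detect some harms.** This stands too. A reader of the low power figures might infer that the trial cannot detect any plausible harm. With no rates in the article that cannot be claimed, and power is 79% to 98% for 10% v 20%, 5% v 15%, 0% v 5% and 10% v 25%.
- **Low power for rare harms is ordinary in a trial sized on efficacy, and an interval adds no events.** True. Chi-squared and Fisher tests are valid and need not be removed. The interval displays the remaining uncertainty, which the p-value hides.
- **Detail of this kind usually sits in the full protocol or SAP.** This holds for the definition of the safety population and for fuller tabulation, which are not pressed here. It does not remove an inference method that the article itself names.

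A reader might also infer that the investigators will take a non-significant test as proof of safety. No section says so, and none sets a safety hypothesis or margin. The Discussion's phrase, "simple, convenient, efficient, and inexpensive, without severe adverse effects", is a cited description of earlier work on acupuncture, not a planned conclusion of this trial.

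**Conclusion.** The point holds in a limited form. The named inference is valid but fits two situations badly.

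- **Acupuncture-only events:** the control rate is zero by design, so the between-arm test is beside the point. The standard error is also uninformative at zero events, when a true rate of up to 1.4% (one-sided 95%) or 1.8% (two-sided) is still compatible with 0 of 208.
- **Uncommon events or modest increases in either arm:** power at 208 per arm is 2% to 24% for 0% v 1–2%, 5% to 18% for 1% v 2–3%, and 14% for 2% v 4%. It is lower at 173 per arm.

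These figures assume two-sided testing at 0.05, all 208 participants per arm contributing, and event rates that the article does not supply. The weakness lies in what would be reported. It does not affect the efficacy analysis, and the article contains no false safety claim.

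**What to change.** Keep the tests and add to the adverse event sentence:

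- the number and percentage of participants with each event type, by arm;
- the risk difference with a score (for example Newcombe) or exact 95% confidence interval;
- for events that can arise only from acupuncture, the incidence in the intervention arm with an exact 95% interval, in place of the standard error and the between-arm test;
- a statement that a non-significant test is not interpreted as absence of harm.

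Name the interval method in advance, because interval and test can disagree with few events: at 5 v 0 of 208, Fisher gives p = 0.061 while the Newcombe interval runs from +0.1 to +5.5 points.

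The cost is a few lines of text and a little more output from the same tables. No new data, participants or visits are needed.

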### Follow-up

After the 12-week treatment period, there is an outpatient 24-week follow-up period. The medical staff will follow up on the participants via telephone. Each participant is contacted once every four weeks, keeping record of the medications and rehabilitation therapies. On the final week of the follow-up period (24 weeks post-intervention), participants will be referred for clinical evaluation in order to assess their functional status, including cognitive function, quality of life, and ADL.

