### Data collection and management

Firstly, screeners are responsible for the acquisition of demographic and baseline characteristic data when the participants are recruited. Outcome assessors play an important role in evaluating the primary and secondary outcomes at baseline, 12 weeks (end of intervention), and 36 weeks (after the 24-week follow-up period). In each center, after the source data has been added to the case report form, two research assistants who are not engaged in either treatment or evaluation will enter those source data into an electronic data capture database through the scientific research management platform of FJTCM. Only the project manager has the right to log into every center’s database. Moreover, a statistical manager will be in charge of initial data organizing, identifying, coding, and converting data to make sure the format is proper for data analysis. Meanwhile, double data entry will be used to promote data quality. All materials related to the participants’ privacy will be kept confidential by the way of coding. Besides, all study documents will be retained securely for five years after completion of the study, and the result of our study will be published in open access journals.

Moreover, this trial has been monitored for safety control by an independent Data and Safety Monitoring Board (DSMB), consisting of two senior therapists and one rehabilitation physician who are experienced in post-stroke cognitive impairment and have no direct involvement in the study. The DSMB is an independent board and is responsible for source data validation, and AE management and reporting. For safety concerns, the DSMB may have the right to recommend termination or modification of the research, according to their clinical judgment.

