However, this protocol design also has potential limitations: for example, it is not a double-blinded, placebo-controlled trial. From the perspective of evidence-based medicine, randomized, double-blind, placebo-controlled trials are the best the trials that render the highest evidence quality, but their feasibility is a major difficulty in non-pharmacological research areas [65]. Considering the ethics and participants’ adherence, blinding seems difficult for acupuncture in a clinical study, thus randomized, double-blinded, placebo-controlled trials may be impossible. Considering these facts, this trial attempts to reduce possible bias through blinding both outcome assessors and data analyst. Further, potential spontaneous recovery at the early stage of stroke may have the confounding effects on the trial.

To conclude, this trial aims to evaluate, under strictly systemized operational and high quality practices, whether a therapeutic regimen of TCM rehabilitation can effectively improve cognitive functions recovery after stroke under strict standard operational practices. If this trial is successfully carried out and renders high quality evidence to support a therapeutic regimen of TCM rehabilitation for PSCI management, this low cost and feasible therapy could be implemented on a larger scale in clinical and community settings.

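### LOCF is the only stated missing-data rule; with no MMSE between baseline and week 12 it scores early dropouts as zero improvement, which lowers power and, if dropout differs by arm, biases the comparison

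*Protocol article*

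**What the plan says.** Statistical methods, protocol article: "Missing data will be imputed by the last observation carried forward rules". No other missing-data method is named. The same section sets the analysis sets: "The analysis of the primary outcome will be expressed by using full analysis set with the principle of intention-to treat and the per-protocol set". For group comparisons, "the t-test or Mann–Whitney U test will be used for continuous variables".

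On timing, Data collection and management describes assessors "evaluating the primary and secondary outcomes at baseline, 12 weeks (end of intervention), and 36 weeks (after the 24-week follow-up period"). Table 1 agrees: MMSE appears at screening, at the pre-treatment evaluation, after the intervention and after follow-up, and nowhere in between. The telephone contacts begin after week 12 and carry no MMSE: "Each participant is contacted once every four weeks, keeping record of the medications and rehabilitation therapies".

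On the expected course, Sample size says "The sample size calculation is based on the improvement of MMSE scores" and that "the mean difference in MMSE scores before and after treatment is three points, with a standard deviation of 1.5". It allows for 20% dropout over the whole study and arrives at 208 per group. The Discussion adds that "potential spontaneous recovery at the early stage of stroke may have the confounding effects on the trial".

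**The concern.** For anyone lost before week 12, the last observation is the pre-treatment score. Carrying it to weeks 12 and 36 fixes that person's improvement at zero, in a trial whose planning figures have patients improving by about 3 points. Participants lost in weeks 13 to 36 are different: they carry the gain seen at week 12.

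Two things are at stake.

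- **Power.** The dropout allowance treats lost participants as leaving the analysis with the effect undiluted. LOCF keeps them in at zero, so the mean difference shrinks and the spread grows.
- **Bias.** If one arm loses more people early, that arm collects more zeros, and the comparison shifts against it even when the treatments are equivalent. Participants and therapists are not blinded and only one arm receives acupuncture, so equal dropout cannot be taken for granted.

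**Working it through.** **Inputs from Sample size.** Mean gain 3 points, SD 1.5, pilot figure 3.52, alpha 0.05, power 90%, 173 per group before dropout, 208 after.

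**The plan's own figure.** n = 2(1.96 + 1.282)² × 1.5² / δ². With δ = 3.52 − 3 = 0.52 this gives 174.9, so 175, close to the stated 173. Taking 3.52 as the between-group difference gives 4 per group, and a difference of 3 gives 6. The effect of 0.52 is thus an inference from the arithmetic, not a figure in the text. The 208 is 173 × 1.2 = 207.6, rounded up.

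**Model of LOCF.** Let d be the share of an arm lost before week 12, unrelated to outcome, and m the mean gain of the rest. The change score after LOCF is zero with probability d and otherwise has mean m and SD 1.5:

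- mean = (1 − d)m
- variance = (1 − d) × 2.25 + d(1 − d)m²

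The test is two-sided at 5% with 208 per arm.

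**Equal early loss, gains 3.52 v 3.00.** At d = 0.20:

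- difference = 0.8 × 0.52 = 0.416
- variances = 1.80 + 0.16 × 12.39 = 3.78 and 1.80 + 0.16 × 9 = 3.24 (SDs 1.95 and 1.80)
- SE = √((3.78 + 3.24)/208) = 0.184
- power = Φ(0.416/0.184 − 1.96) ≈ 62%

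Observed data alone would be 166 per arm with SD 1.5 and power about 88%.

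| Lost before week 12, each arm | LOCF difference | Power, LOCF | Power, observed data |
|---|---|---|---|
| 5% | 0.494 | 87% | 93% |
| 10% | 0.468 | 79% | 92% |
| 15% | 0.442 | 70% | 90% |
| 20% | 0.416 | 62% | 88% |

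**Unequal early loss, no true effect.** With a common gain m, bias = m × (difference in dropout shares). For 15% v 25% and m = 3:

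- bias = 3 × 0.10 = 0.30
- variances = 3.06 and 3.375, so SE = √(6.435/208) = 0.176
- rejection probability ≈ 40%

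| Early loss by arm | Common gain | False difference | False-positive rate |
|---|---|---|---|
| 9% v 11% | 3 | 0.06 | about 7% |
| 8% v 12% | 3 | 0.12 | 11% |
| 15% v 20% | 3 | 0.15 | 14% |
| 15% v 25% | 3 | 0.30 | 40% |
| 15% v 25% | 2 | 0.20 | 26% |
| 15% v 25% | 1 | 0.10 | 11% |

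Analysis of observed data keeps the error near 5% in these cases, because loss is assumed unrelated to outcome. The direction follows the arm that loses more: with a true effect of 0.52 and 25% lost on intervention against 15% on control, the LOCF difference is 0.75 × 3.52 − 0.85 × 3.00 = 0.09 and power is about 7%.

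**Check.** Simulated t-tests (8,000 runs) gave 61% power for 20% loss in each arm and 39% error for 15% v 25% under the null, in line with the formulas.

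**The case against.** A reader might infer that the trial will have 62% power, or a 40% false-positive rate. The documents do not support either as a forecast.

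- **Timing.** The 20% dropout covers the whole study. Putting all of it before week 12 is the ceiling.
- **Split by arm.** None is given. Both arms attend the same 30-minute, five-day schedule for 12 weeks, and acupuncture takes place within the cognitive-training session, so a ten-point gap is only a possibility.
- **Gain of dropouts.** The 3 points are a before-after change with treatment. Nothing says what someone who leaves early would gain; if that is nothing, the bias disappears. The spontaneous-recovery remark is tentative, and patients may enter up to a year after stroke. It would therefore overreach to say that the protocol's own figures prove zero to be wrong for these patients.
- **Outcome scale.** The trial is sized on improvement, but the testing sentence can be read as comparing scores at each visit. With an assumed baseline SD of 2 to 5 points, unrelated to gain, the 15% v 25% null case gives about 21% down to 9% error.
- **Effect size.** Read literally as 3.52 points between groups, power would stay near 100% even under LOCF, but that reading cannot produce 173 per group.
- **Analysis set.** If the full analysis set required a post-baseline MMSE, early dropouts would not be imputed at all. No such condition is stated, and the intention-to-treat wording points the other way.

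An unseen analysis plan may add sensitivity analyses, so their absence from the article is not the complaint. The per-protocol analysis is a second population, not another missing-data method.

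These points limit the size and the certainty. They do not make LOCF a sound primary rule: 5% early loss in each arm still takes power from 93% to 87%, for no gain.

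**Conclusion.** The point stands as a weakness in a rule that the protocol fixes, and it should be fixed. Given the visit schedule and an intention-to-treat set that keeps early dropouts, LOCF assigns them zero improvement.

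On change scores, with an inferred effect of 0.52 and loss unrelated to outcome, power falls to about 87%, 79% or 62% at 5%, 10% or 20% early loss per arm. Bias arises only if early loss differs between arms and the dropouts would have improved. It can run in either direction, and the false-positive rate then ranges from little above 5% to about 40% over the splits examined. How much of this applies depends on the timing and split of dropout, which the protocol does not give, so it is not established that the primary conclusion will be wrong.

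**What to change.** Replace the LOCF sentence. Make the primary analysis a mixed model for repeated measures on MMSE at weeks 12 and 36, with baseline MMSE, centre, arm, visit and visit-by-arm, or use multiple imputation by arm. Add a delta-adjusted or reference-based sensitivity analysis for dropout that depends on the unseen outcome. Keep LOCF, if at all, as a labelled sensitivity analysis.

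The cost is a change of wording and a little more analysis work; no new data are needed. The price in assumptions is that the primary analysis rests on data being missing at random, which is why the sensitivity analysis belongs with it.
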